## Abstract

**Background:**

Remote monitoring of patients with New York Heart Association (NYHA) functional class III heart failure (HF) using daily transmission of pulmonary artery (PA) pressure values has shown a reduction in HF-related hospitalizations and improved quality of life in patients.

**Objectives:**

PASSPORT-HF is a prospective, randomized, open, multicenter trial evaluating the effects of a hemodynamic-guided, HF nurse-led care approach using the CardioMEMS™ HF-System on clinical end points.

**Methods and results:**

The PASSPORT-HF trial has been commissioned by the German Federal Joint Committee (G-BA) to ascertain the efficacy of PA pressure-guided remote care in the German health-care system. PASSPORT-HF includes adult HF patients in NYHA functional class III, who experienced an HF-related hospitalization within the last 12 months. Patients with reduced ejection fraction must be on stable guideline-directed pharmacotherapy. Patients will be randomized centrally 1:1 to implantation of a CardioMEMS™ sensor or control. All patients will receive post-discharge support facilitated by trained HF nurses providing structured telephone-based care. The trial will enroll 554 patients at about 50 study sites. The primary end point is a composite of the number of unplanned HF-related rehospitalizations or all-cause death after 12 months of follow-up, and all events will be adjudicated centrally. Secondary end points include device/system-related complications, components of the primary end point, days alive and out of hospital, disease-specific and generic health-related quality of life including their sub-scales, and laboratory parameters of organ damage and disease progression.

**Conclusions:**

PASSPORT-HF will define the efficacy of implementing hemodynamic monitoring as a novel disease management tool in routine outpatient care.

**Trial registration:**

ClinicalTrials.gov; NCT04398654, 13-MAY-2020.

**Graphical abstract:**

[figure not shown]

**Supplementary Information:**

The online version contains supplementary material available at 10.1007/s00392-022-01987-3.

## Introduction

Heart failure (HF) is a grave clinical syndrome characterized by complex treatment regimens, frequent rehospitalizations, and impaired quality of life [1]. For Germany, the annual incidence of HF was 655 per 100,000 persons estimated from health-care claims data sets [2], with an overall prevalence of 5.3% among adults [3]. Decompensation of HF in Germany accounts for more than 1,000,000 hospital admissions per year [2, 4], despite continuously improving treatment options [1]. Better implementation of and adherence to guideline-directed pharmacotherapy are regarded pivotal factors mediating more favorable outcomes [1, 5–7]. More than 90% of patients hospitalized for HF present with cardiopulmonary congestion, which develops secondary to an increased pulmonary arterial (PA) pressure. As this signal (or a clinical surrogate) is difficult to detect in routine care, electrode- and battery-free sensors have been developed that can wirelessly transmit PA pressure values from the patient's home by remote access [8].

The multicenter CHAMPION trial investigated 550 patients in New York Heart Association (NYHA) class III, who had been hospitalized within the previous year due to HF [9]. All patients were managed by dedicated HF staff. Care in the intervention arm was enhanced by utilizing information on PA pressure derived daily from a CardioMEMS™ sensor and transmitted wirelessly to the HF staff. Compared to controls, patients managed by PA pressure-guided care experienced 33% fewer HF-related hospitalizations within 15 months of follow-up [9]. Further, PA pressures were reduced, the proportion of patients hospitalized for HF decreased, and quality of life improved [9]. These effects were replicated when the former control group was also switched to CardioMEMS™-based remote care (risk reduction 48%) [10]. The 2016 ESC Guidelines for the diagnosis and treatment of acute and chronic HF assigned a IIb recommendation to the deployment of a CardioMEMS™ HF-System in HF patients meeting the selection criteria of the CHAMPION trial [11]. The European non-randomized MEMS-HF follow-up study assessed the safety and feasibility of the CardioMEMS™ HF-System in 234 NYHA class III patients [12]. MEMS-HF found that care enriched by remotely obtained PA pressure values was associated with an 80% (69%) reduction in HF (all-cause) hospital readmissions [13].

Although the CardioMEMS™ HF-System has demonstrated its safety and efficacy, all randomized evidence was generated in the USA. The German health-care system assigns different responsibilities to various care sectors without obligatory provision of a synchronized care plan including documentation and structured communication between care providers. Further, dedicated non-physician HF staff, e.g., HF nurses supporting patients and relatives during their iterative contacts with inpatient and outpatient care, are not yet part of clinical routine. The PASSPORT-HF trial was therefore initiated to prospectively investigate the efficacy of 12 months of PA pressure-guided remote HF management in HF patients with NYHA class III symptoms on clinical end points, within the German health-care system.

## Patients and methods

### Legal framework

The PASSPORT-HF trial was commissioned by the German Federal Joint Committee (G-BA), i.e., the highest decision-making body representing physicians, dentists, hospitals and health insurance funds, as part of a conditional coverage program in Germany for health-care-related costs. Interventions yielding benefits in trials executed under the auspices of the G-BA are to be implemented and reimbursed as part of routine care. As such, the G-BA provided the framework for the trial, outlined the PASSPORT-HF study design, and defined the primary end point. The G-BA provided funding for study conduct and case payments. Further, the G-BA passed regulations ensuring cost coverage by health insurance companies for the CardioMEMS™ HF-System, the dedicated patient electronics unit, and the post-discharge care both in the intervention and control arm, for duration of the trial.

### Study design, eligibility criteria for study sites and patients, and main hypothesis

PASSPORT-HF is an open, prospective, randomized, multicenter clinical trial that will enroll 554 patients with chronic HF, predominantly in NYHA functional class III within the last 30 days and hospitalized for HF at least once in the 12 months prior to enrollment. Inclusion and exclusion criteria are shown in Tables 1 and 2. Diagnosis of HF is made by the study physician according to the criteria of the 2016 ESC Guidelines for Acute and Chronic Heart Failure [1, 11]. In total, about 50 German hospitals, cardiology practices, and medical service centers, distributed across all German federal states, will participate (Fig. 1; Supplemental Table S1). To qualify for an investigational site, specifically trained HF nurses or HF care experts must be available, and three CardioMEMS™ sensors must have been implanted and calibrated successfully. The primary hypothesis of the PASSPORT-HF trials states that the CardioMEMS™ HF-System applied in addition to basic HF care will reduce all-cause mortality and HF-related hospitalizations in patients with NYHA class III chronic HF.

**Table 1 Tab1:** Inclusion criteria

1	Written informed consent received from the patient or a legal representative after the information has been provided
2	≥ 18 years of age
3	Predominant symptoms in NYHA Stage III in the 30-day period prior to consent to the study
4	Objectified HF diagnosis for more than 3 months
5	Hospitalization within 12 months prior to inclusion due to deterioration of HF symptoms
6	Able to tolerate dual antiplatelet therapy or anticoagulation therapy for 1 month after sensor implantation
7	Patients with reduced left ventricular ejection fraction (LVEF) ≤ 40% (assessed within 6 months prior to inclusion) must be treated with guideline-compliant HF pharmacotherapy; if one class of guideline-compliant medication is not tolerated, appropriate documentation must be supplied; patients must receive and tolerate at least one class of guideline-compliant medication; if no guideline-compliant medication is tolerated at all, the patient may not participate in the study
8	In patients with preserved LVEF (> 40%; assessed within 6 months prior to inclusion), comorbidities must be treated in accordance with guideline-compliant medication
9	Chest circumference (measured at axillary level) of less than 165 cm if BMI > 35 kg/m^2^
10	Willing and mentally and physically able to meet the requirements for follow-up and long-term basic care (this includes the long-term willingness of the patient, and of their relatives where relevant, to participate in PA pressure-based monitoring)
11	Appropriate domestic situation, defined as being accessible by telephone (via fixed or mobile network)^a^
12	For the intervention group: implantation is only performed if the diameter of the pulmonary artery branch intended for implantation is ≥ 7 mm (assessment will be made during the right heart catheterization)

**Table 2 Tab2:** Exclusion criteria

1	Enrollment in another study with an active treatment arm
2	Severe cardiovascular event (e.g., myocardial infarction, open heart surgery, stroke, CRT implantation) in the 2 months prior to admission
3	Therapy-refractory heart failure in ACC/AHA stage D or new therapies that have taken place or are planned in the next 12 months (e.g., implantation of a left ventricular assist system / transplantation)
4	Active infection
5	History of recurrent (> 1 episode) pulmonary embolism and/or deep vein thrombosis
6	Continuous or intermittent chronic inotropic therapy
7	Estimated glomerular filtration rate (eGFR) < 25 ml/min
8	Life expectancy (according to the study physician's assessment) < 12 months
9	Severe, unrepaired congenital heart defect that would prevent implantation of the sensor
10	Severe valve vitium with planned intervention in the next 3 months
11	Presence of a mechanical right heart valve
12	Mental disorder that presumably (in the opinion of the study physician) has a negative impact on patient compliance or consent
13	Failure of the coordinating physician to approve if the patient is enrolled in an HF disease management program or comparable case management program^a^
14	Women of childbearing age with a positive pregnancy test at the time of inclusion

**Fig. 1 Fig1:**
[figure not shown]
Participating centers in Germany

### Randomization

At the baseline visit, after signing the written informed consent, patients will be randomized centrally 1:1 into basic HF care plus CardioMEMS™ PA-guided remote care versus basic HF care alone. Randomization is done block-wise, stratified by study site. Crossover is allowed per clinical investigation plan and will not lead to termination of study participation. After randomization, the CardioMEMS™ sensor is required to be implanted within 14 days. A second informed consent form will be signed by patients in the intervention arm for the use of the Merlin.net™ website, where transmitted sensor values are being stored.

### CardioMEMS™ HF-System

All patients randomized into the intervention arm receive the CardioMEMS™ HF-System. It consists of three elements: (1) the PA pressure sensor (implanted into the distal branch of the descending pulmonary artery during right heart catheterization procedure via femoral vein approach), (2) the patient electronics system (a pillow placed in the patient's home environment including an electronic device with receiving and transmitting functions), and (3) the patient database (Merlin.net™ website), where the incoming PA pressure measurements are stored and visualized in trend graphics (Fig. 2) [9]. The device is CE marked for use in chronic HF patients in NYHA class III and with at least one HF hospitalization in the previous year [9]. Transmitted information consists of systolic, mean, and diastolic PA pressure trend information including the PA pressure waveforms in addition to pressure-derived heart rate. This information becomes instantly accessible and visible after measurement for review by clinicians and nurses via the Merlin.net website. A study-specific standard operating procedure has been produced serving as treatment guideline, particularly with regard to handling PA pressure values as possible triggers or supporting information for optimizing guideline-compliant HF treatment.

**Fig. 2 Fig2:**
[figure not shown]
The CardioMEMS™ HF-System. The CardioMEMS pulmonary artery (PA) pressure sensor is shown (top, left), with its placement in the left PA. The sensor has a vertical orientation if the patient sits upright. After implantation, while still in hospital, the patient is instructed by trained staff how to position him/herself on the pillow that contains the measurement unit and measure and transmit the PA pressures once daily. The transmitted values can be accessed via a safe website by the heart failure nurse. Individual PA measurements (with tracings, see bottom right) and PA trends over time are visualized on the dashboard, allowing to interpret values in the context of supplementary information

### Basic HF care

In the PASSPORT-HF trial, basic care is facilitated by HF nurses and comprises the five components summarized in Table 3.

**Table 3 Tab3:** Definition of basic care in the PASSPORT-HF trial, delivered by specialized HF staff

Component	Description
Patient training at study start	An educational session with specialized HF staff while the patient is still in hospital; with the option to repeat educational segments during subsequent telephone calls, if required
Patient manual	An illustrated brochure handed out at study start; it informs on HF symptoms, medication, and gives advice regarding self-care, life-style adjustments, and emergency measures; during telephone follow-up calls, specialized HF staff can refer to its content
Symptom calendar	Booklet for daily self-recording of the patient´s body weight, blood pressure, heart rate, and symptoms
Repetitive structured telephone contact	Weekly calls in the first month after study initiation, then bi-weekly calls for patients in NYHA class III/IV, and 4-weekly calls for patients in NYHA class I/II for the remainder of the study period; contents of these contacts are documented in a structured fashion; a modified 14-item questionnaire [5] will be used addressing general health status, most recent self-measured values, indicators of deteriorating HF, well-being, and (changes in) medication; all educational elements relate to recommendations listed in the The German National Disease Management Guideline “Chronic Heart Failure” (*Nationale VersorgungsLeitlinie Chronische Herzinsuffizienz,* https://www.leitlinien.de/nvl/herzinsuffizienz)
Usual medical care	Treatment of HF and concomitant diseases by means of guideline-directed therapy and routine pathways established at the respective site or region

### CardioMEMS™ HF supported care

In the intervention arm, the care concept includes all elements of basic care detailed in Table 3 and is further enhanced by using the PA pressure information transmitted daily via the CardioMEMS™ HF-System. After implantation and prior to hospital discharge, the HF nurse instructs the patient on the use of the measurement unit, frequency of measurements and transmissions, meaning of reaching optimal PA pressure targets and importance of euvolemia, intensified pharmacotherapeutic regimens to reach PA pressure targets, and the mode of telephone interaction and feedback loops that is now implemented for the study period (Fig. 3).

**Fig. 3 Fig3:**
[figure not shown]
PASSPORT-HF trial follow-up scheme. R: central randomization 1:1, stratified by study site. NYHA, New York Heart Association; PA, pulmonary artery

### Clinical study flow

In the light of the findings of the MEMS-HF study [12], we assumed an inclusion rate of one subject per month and site. With approximately 45 (40–50) enrolling sites, it is expected that the period of study enrollment will be around 18 months. Taking into account an interval for the initiation of the sites (approx. 6 months), this results in a planned enrollment phase of 24 months. All patients will be followed for 12 months. The follow-up visits are scheduled at 3, 6, and 12 months following randomization.

#### Patient visits

At the baseline visit, demographic data, medical history and current medication are recorded. Baseline assessment also includes a physical examination, NYHA functional class assessment, detailed laboratory evaluation, and questionnaires addressing quality of life and psycho-emotional domains (Kansas City Cardiomyopathy Questionnaire [KCCQ]; European Quality of Life 5 Dimensions 5-Level Version [EQ-5D-5L]; Patient Health Questionnaire Depressive Symptoms [PHQ-9]; Generalized Anxiety Disorder Scale [GAD-7]). For the intervention group, procedural details on the implantation procedure (including calibration of the PA sensor; adverse events and device/system-related complications) are documented. A standardized echocardiographic examination protocol is desirable, but for pragmatic reasons not obligatory. Investigations are repeated during outpatient visits after 3, 6, and 12 months (for details see Table S2).

#### Impact of the COVID-19 pandemic

Follow-up visits might require adjustment during the COVID-19 pandemic according to potential restrictions imposed by the government and consequences concerning the per-protocol conduct of the study. These may extend to travel restrictions, visiting bans regarding the investigational sites, or the study patient’s lacking willingness to visit the investigational site for the stipulated follow-up visits. If a study participant cannot or is unwilling to visit the investigational site in person, efforts will be taken to complete remotely (i.e., via telephone call) as much of the follow-up information as possible. Patient questionnaires will be sent to the patient by mail. Laboratory values substituting the per-protocol central laboratory can be obtained from the patient’s treating physician.

### Outcome measures

#### Primary end point

The primary efficacy end point is a composite of all-cause death and unplanned HF hospitalizations 365 days after randomization. Unplanned HF-related hospitalization is defined as an unplanned overnight hospitalization, the main reason for which is decompensated HF. Hospitalization due to HF also includes hospitalization resulting from the investigational intervention (e.g., bleeding). The primary safety end point is freedom from device/system-related complications (DSRC) in patients in whom an implantation has been tried or completed, or sensor failure, within a time frame of 12 months.

#### Secondary end points

The major secondary end point is the change in quality of life scores measured after 6 and 12 months using the Kansas City Cardiomyopathy Questionnaire (KCCQ). The KCCQ is a well-established measure for quality of life in HF patients and has been applied as end point in pharmacotherapeutic and device trials [14]. Additional secondary end points include general health-related quality of life (EQ-5D-5L at 6 and 12 months), mortality at 12 months (HF-related, cardiovascular, all cause), unscheduled hospitalizations (HF-related, cardiovascular, all cause, number of days alive and out of hospital), adverse events and symptoms of HF (Table 4).

**Table 4 Tab4:** Study end points

Primary efficacy end point	Composite of the number of unplanned HF-related rehospitalizations or all-cause mortality 365 days after randomization (12-month time)
Primary safety end point	1. Device/system-related complications (DSRC) of the patients as a result of the attempted or successful implantation of an CardioMEMS™ sensor at the 12-month time point and 2. Freedom from sensor failures at the 12-month time
Secondary end points	(A) Health-related quality of life Major secondary: changes in quality of life (QoL) measured using the Kansas City Cardiomyopathy Questionnaire (KCCQ) scores (TSS, OSS, CSS), after 6 and 12 months Changes in QoL scores measured after 6 and 12 months using Euro-QoL-5D (B) Mortality HF-related mortality in the 12-month period Other cardiovascular mortality in the 12-month period Non-cardiovascular mortality in the 12-month period All-cause mortality in the 12-month period (C) Unplanned hospitalizations HF-related hospitalizations in the 12-month period Other cardiac-related hospitalizations in the 12-month period Non-cardiovascular-related hospitalizations in the 12-month period All-cause hospitalizations in the 12-month period Number of days alive and out of hospital in the 12-month period (D) Adverse events Frequency of adverse events in the 12-month period Frequency of serious adverse events in the 12-month period (E) Symptoms of heart failure and psychometric assessments Patient-reported symptoms of heart failure assessed by the KCCQ Symptoms Score Unscheduled HF-related hospitalizations HF-related mortality Days alive and out of hospital Laboratory parameters for organ damage and disease progression Change in symptom burden of anxiety (GAD-7) at 6- and 12-month time points Change in symptom burden of depressive symptoms (PHQ-9) at 6- and 12-month time points (F) Care-related aspects Patient adherence in the intervention group in terms of obtaining PA pressure readings, at 6 and 12 months Change in PA pressure values at 6 and 12 months, based on the area under the curve Number of adjustments made within each guideline-recommended substance class and their underlying reasons Change in drug dose (equivalent dosages) of maximum guideline-recommended substance class received, at 6 and 12 months Rate of documented atrial and ventricular arrhythmias over a 12-month period Laboratory measures of organ damage and disease progression: renal and cardiac biomarkers with associated changes Health economic data (resource use) at 6- and 12-month time points

### Sample size calculation

For PASSPORT-HF, we defined inclusion and exclusion criteria comparable to the CHAMPION trial and anticipated similar clinical effects [9, 10]. Accordingly, a rate of 0.84 events per patient-year was assumed for the primary efficacy end point in the control arm, and a rate of 0.58 events per patient-year in the intervention arm (corresponding to a hazard ratio of 0.69). Assuming a dropout rate of 20%, this yielded a total sample size of 554 patients for the study (227 patients per arm, assuming alpha = 2.5% for one-tailed testing, 1-beta = 90%). Accordingly, at least 442 patients, i.e., 221 patients per arm, are required for the proposed analysis using the Anderson–Gill model.

### Data analysis and analysis populations

#### Descriptive analyses

Data will be summarized using univariable statistics (number, mean, standard deviation, median, maximum, minimum) or frequency (absolute number, percentage). Between-group comparisons for baseline characteristics will be performed with Pearson’s Chi-squared test for categorical variables and Mann–Whitney or Wilcoxon tests for continuous variables.

#### Analysis populations

The primary hypothesis will be analyzed using the full analysis set based on the intention-to-treat (ITT) principle, i.e., on the data from all randomized patients (excluding only patients from the intervention/control group who terminate the study before the first implantation attempt; if the implantation is unsuccessful, the patient, however, will be included in the analysis set). A supportive per-protocol analysis of the primary hypothesis is performed (efficacy sample), including all who completed the study according to the clinical investigation plan and excluding patients violating the inclusion or exclusion criteria upon enrollment as well as patients with major deviations from the clinical investigation plan.

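### The primary set is called intention-to-treat but drops patients who leave before a first implantation attempt, a time point that controls do not have

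*Protocol article*

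**What the plan says.** Under Analysis populations the article states: "The primary hypothesis will be analyzed using the full analysis set based on the intention-to-treat (ITT) principle, i.e., on the data from all randomized patients". A bracket in the same sentence then makes one exception, "excluding only patients from the intervention/control group who terminate the study before the first implantation attempt", and adds that "if the implantation is unsuccessful, the patient, however, will be included in the analysis set". The only other analysis named there for the primary hypothesis is per-protocol.

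Three other places bear on how this rule works:

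- Randomization: "patients will be randomized centrally 1:1 into basic HF care plus CardioMEMS™ PA-guided remote care versus basic HF care alone". No implantation is planned for controls, although crossover is permitted.
- Randomization: "After randomization, the CardioMEMS™ sensor is required to be implanted within 14 days". The attempt can therefore come up to two weeks after allocation.
- Primary end point: the outcome is a "composite of all-cause death and unplanned HF hospitalizations 365 days after randomization". The clock starts at randomisation, not at implantation.

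**The concern.** The exclusion is decided after randomisation and hangs on a step that belongs to one arm's strategy. Naming both groups does not make it symmetric, because the article does not say what stands in for the attempt in a control. One reading leaves controls almost untouched while early leavers go from the device arm. The other removes every control who ends participation, since for nearly all of them no attempt ever comes.

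The trial is open, and only device patients face an invasive procedure soon after allocation. Leaving before the attempt can therefore depend on both the arm and the patient's prognosis. That is the condition under which dropping such patients distorts a randomised comparison. Because follow-up starts at randomisation, the gap before the attempt lies inside the end point window. The article does not say whether a death in that gap counts as ending participation. If it does, primary events would leave the device arm.

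This is the primary population of a trial meant to decide on implementation in routine care, and the article names no analysis that keeps everyone randomised.

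**Working it through.** **Inputs from the article (Sample size calculation; Randomization).** Control rate 0.84 and device rate 0.58 events per patient-year; one-sided alpha 2.5%, power 90%; dropout 20%; 221 patients per arm for analysis, 554 in total; up to 14 days from randomisation to implantation.

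**The plan's own figures.** The Poisson rate-difference formula gives (1.960 + 1.282)² × (0.84 + 0.58) / (0.84 − 0.58)² = 220.7, so 221 per arm. Then 221 / 0.80 = 276.25, so 277 per arm and 554 in total. The 442 and 554 reproduce and are not in dispute. I use 277 per arm; the printed 227 does not fit 554 (2 × 227 = 454), which is a separate matter.

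**Assumptions that the article does not supply.** Let p be the share of the device arm excluded and m the event rate of those patients relative to the arm average. Assume no true device effect and no exclusion of controls. Then:

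- Null ratio = (1 − pm) / (1 − p).
- SE of the log ratio = √[(1/0.84 + k)/277 + (1/r + k)/(277(1 − p))], where r = 0.84 × ratio and k is the dispersion (0 for Poisson).
- One-sided error in favour of the device = P(Z > 1.96 − |log ratio| / SE).

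**An anchor for p.** Dropout of 20% spread evenly over the year gives 0.20 × 14/365 = 0.77% within 14 days, or 277 × 0.0077 = about 2 patients.

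**Worked case.** With p = 5%, m = 2 and k = 0, the ratio is 0.90/0.95 = 0.947, its log −0.054 and the SE 0.095. The shift is 0.57 and the error 8.2%.

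| Excluded (of 277), m = 2 | Null ratio | Error, Poisson | Error, k = 1 |
|---|---|---|---|
| 0.77% (about 2) | 0.992 | 3.0% | 2.9% |
| 2% (about 6) | 0.980 | 4.1% | 3.6% |
| 5% (about 14) | 0.947 | 8.2% | 6.2% |
| 10% (about 28) | 0.889 | 22% | 14% |

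With m = 1 the ratio is 1.00 and the error 2.5% in every row. If the doubled rate is measured against the remaining patients instead of the arm average, the Poisson errors for 2%, 5% and 10% are 4.0%, 7.4% and 16%.

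**What retention alone recovers.** Keep the leavers but censor them at 14 days. At p = 5% and m = 2 this adds 277 × 0.05 × 14/365 = 0.53 patient-years and 0.53 × 2 × 0.84 = 0.89 events. The ratio becomes 0.949 and the Poisson error about 7.9%. At p = 10% they become 0.894 and 21%. Most of the distortion is thus informative early dropout, and it disappears only if leavers are followed.

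**Literal reading for controls.** At 20% dropout, up to 0.20 × 277 = about 55 controls would go. If their rate were 1.5 to 2 times that of the remaining controls, the null ratio would be 0.8 + 0.2 × 1.5 = 1.10 to 0.8 + 0.2 × 2 = 1.20, against the device. This too treats the removed patients as if they would have contributed a full year.

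**The case against.** The strongest reply is that the trigger is narrow. Only patients who end their participation are excluded, not everyone left without a sensor, and failed implantations stay in. That stands, and it rules out several stronger inferences:

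- A reader might take the additional consent ("A second informed consent form will be signed by patients in the intervention arm") and the artery check ("For the intervention group: implantation is only performed if the diameter of the pulmonary artery branch intended for implantation is ≥ 7 mm") as exits from the analysis. Neither is. That consent concerns the data website, and nothing says that refusing it ends participation. The diameter rule limits implantation and does not remove the patient from the study.
- A reader might infer that early deaths are dropped. The article does not say so; it leaves the question open.
- At 0.84 per year, 277 × 0.84 × 14/365 = about 9 primary events per arm fall in the 14 days. These are all the events in the window, not the events that would be lost. A patient admitted for heart failure who stays in the study is still counted.
- A reader might call the attempt something that only the device arm can have. Crossover is allowed, so a control could be implanted. What holds is that no attempt is scheduled for controls.

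It is also fair that exclusions of 5 to 10% have no support in the article, and that the full clinical investigation plan may define a counterpart for controls. The second cannot be checked here. As published, the rule names the control group and ties it to an event that controls are not due to have.

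**Conclusion.** The point holds as a defect of definition. The set described is not intention-to-treat and is not symmetric between the arms on either reading. Its effect cannot be sized from the article and may well be small. Evenly spread dropout and a doubled event rate among leavers give a null ratio near 0.99 and a one-sided error near 3.0%. Errors of 6 to 8% need an assumed 5% exclusion, and those of 14 to 22% an assumed 10%. All of these rest on device-arm exclusion only and on leavers at twice the average risk. A flat statement that the type I error is wrong, or that the bias favours the device, would go too far: at average risk there is no bias, and the literal reading for controls can push the other way. The reason to act is that the primary population is ambiguous and contradicts its own label, while the correction is cheap.

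**What to change.** Delete the bracketed exclusion. Define the full analysis set as all randomised patients, analysed in the allocated arm from the date of randomisation, whether or not an implantation was attempted. Count every death and every unplanned heart failure hospitalisation from day 0. Follow patients who leave early to day 365 where their consent allows, and otherwise censor them at last contact. The follow-up is essential, because retention with early censoring changes little. Keep the attempted-implantation criterion for the device safety set, where the primary safety end point already uses it. Show the present set as a sensitivity analysis if wanted, with the control counterpart written out.

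The cost is one sentence, follow-up of what may be only a few early leavers, and a slight dilution of the estimated effect. The 442 patients for analysis, the 554 to enrol and the significance level do not change.
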